### Additional Exploratory Analysis

The relationship between sleep measures, sleep habits and demographic data will be evaluated with Pearson (r) correlations. Those will provide information to prove the hypothesis that acknowledgment and application of adequate sleep habits may improve sleep on children. Furthermore, it will allow us to identify if any demographic data (e.g., family incomes, education levels) is related to sleep parameters and sleep habits.

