Additionally, secondary effects of such condition can be identified in the child’s family, as the following: negative impact on sleep quality, daytime functioning and subjective well-being; and the presence of depressive symptomatology, fatigue, stress, and conjugal conflicts (Meltzer and Mindell, 2007; Sadeh et al., 2010; Kelly and El-Sheikh, 2011). Similarly, children and teenagers’ sleep patterns is associated with parental sleep patterns and family functionality (Kalak et al., 2012; Bajoghli et al., 2013; Urfer-Maurer et al., 2017), especially on infants (Brand et al., 2009). This bi-directional association could be explained by: (1) influence of socioeconomic status (SES) in functionality and environment, (2) parenting style and psychological function of parents, and (3) correspondence of inadequate sleep habits between parents and their child (Bajoghli et al., 2013; Urfer-Maurer et al., 2017).

Insufficient and irregular sleep could be influenced in part by poor sleep hygiene (Mindell et al., 2015; Brockmann et al., 2016; Brambilla et al., 2017). Study with caregivers reports indicate that sleep hygiene is associated with how well children ages 0–10 years sleep (Mindell et al., 2009). Sleep hygiene practices includes a set of behavioral and environmental recommendations on sleep environment, sleep routine and daytime activities with the aim of promoting healthy sleep (Irish et al., 2015).

Common sleep hygiene practices in the sleep environment include providing a comfortable bedroom, without excessive noise or distracting stimuli, and with adequate temperature and luminosity. Promotion of a sleep routine is significantly important for children, as it helps to maintain consistent sleep schedules on school days and weekends, and to avoid sleep deprivation. Additionally, a bedtime routine could be composed by activities that help prepare the child to fall asleep, such as: reading, talking about the day, bath time and story-telling (Irish et al., 2015; Allen et al., 2016).

The National Sleep Foundation’s recommendations on sleep duration indicate that school-age children, focus of this study, should sleep in between 9 and 11 h. Still, in this age it is observable widespread use of technology, with increased use of mobile devices (Hirshkowitz et al., 2015; Brockmann et al., 2016). There is as well an increasing demand of their time on school, extracurricular and social activities (Kelly and El-Sheikh, 2011).

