In this way, our research team developed a serious game based on recommendations of Sleep Hygiene, named “Perfect Bedroom: learn to sleep well.” Considering the potential benefits of these approaches taken together, we hypothesized that an intervention with the serious game “Perfect Bedroom: learn to sleep well” may be helpful to modify: (a) inappropriate sleep habits related to irregular sleep and wake times, (b) inadequate sleep environment and pre-sleep activities, and consequently (c) improve sleep parameters, such as sleep duration and sleep efficiency, and decreasing sleep latency somnolence levels.

Therefore, an experimental, prospective and quantitative study will be used to compare effects of game application by in change of habits and parameters of sleep, measured by objective and subjective tools, as well as assessing the player’s decisions as a result of playing this serious game, with the inclusion of an ecological assessment about sleep routine and bedroom organization by children. As far as our knowledge goes this is the first intervention that included a serious game to promote healthy sleep habits to children.

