#### UNESP Sleep Habits and Hygiene Scale (Child Version)

This scale contain 16 questions and will be used to evaluate characteristics of children’s sleep, according to four indicators that are considered causal to sleep hygiene: sleep routine (activities realized before bedtime); physiological alert (diurnal habits that would promote excitement or physical discomfort near to bedtime); cognitive/emotional aspects (indicators of emotional regulation and wellbeing before bedtime) and sleep environment (adequate sleeping environment in terms of temperature, comfort, and organization) (Pires et al., 2012). Each item is assessed on a five point of frequency scale from “never – no day” to “always – every day.” Furthermore, the scale contains five questions to evaluate bedtime resistance and daytime somnolence, assessed also on a five-point scale of frequency. Higher scores indicate worst habits of sleep hygiene. This has been empirically validated for use in Brazil.

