Presence of electronic media in the bedroom (e.g., television, video game, and computer) and the use of them next to bedtime are related to late bedtime and decreased sleep duration. In addition, children that sleep next small screens (e.g., smartphones) relate impacts in perception of insufficient rest, probably caused by waking up due to notifications on the small screen (Cain and Gradisar, 2010; Falbe et al., 2015). The opposite is also true, and children that do not have electronics in the bedroom report more hours of sleep. Other factors related to the bedroom are also relevant, such as providing a comfortable bedroom and conditions to sleep, but this is challenging for families of low SES (Chung et al., 2014; Bagley et al., 2015).

Our serious game includes recommendations in sleep environment, but just the game is not enough to help children in families with low-incomes. Provide conditions, such as quiet and dark bedroom and comfortable bed, depends on the neighborhood that the families live and their incomes. Thus, subsequent interventions should include actions to help these families provide a comfortable bedroom, such as Time’s Beds for Kids in EUA (Mindell et al., 2016).

It stands-out that in Brazil did not exist, in our knowledge, any questionnaire adapted and validated to evaluate the chronotype of children with ages between 7 and 8 years, as different types have influences on the presence of sleep disorders and accentuate inadequate sleep habits (Jafar et al., 2017), so chronotype influence was not assessed in this protocol.

Other pitfall that could be noted, is the consideration that parent’s reports may be influenced by social desirability, indicating good sleep hygiene practices instead of the real situation. Another important challenge is to promote parental involvement, since previous researches indicated a decrease in participation over the evaluation periods (Jones et al., 2013; Wilson et al., 2014; Mindell et al., 2016). In this way, we proposed follow-up meetings with parents to minimize this decrease on participation.

Although in this protocol efficacy measures in evaluation will be limited to sleep habits and patterns, the promotion of optimal sleep has consequences in multiples domains (e.g., cognitive, health, temperament) that are sometimes completely forgotten in sleep programs interventions (Blunden, 2017). Thus, future studies should include other outcomes to evaluate efficacy, such as cognitive and academic performance.

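### Unadjusted Pearson correlations cannot support the exploratory claim that applying good sleep habits may improve children's sleep

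*Protocol article*

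**What the plan says.** All references are to the Protocol article.

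- Under the heading "Additional Exploratory Analysis", the method is given in one sentence: "The relationship between sleep measures, sleep habits and demographic data will be evaluated with Pearson (r) correlations". No covariates, time point or handling of arm are stated.
- The next sentence gives the inference: "Those will provide information to prove the hypothesis that acknowledgment and application of adequate sleep habits may improve sleep on children".
- Demographic variables appear only as further things to correlate, to "identify if any demographic data (e.g., family incomes, education levels) is related to sleep parameters and sleep habits". They are not used as adjustment variables.
- The Introduction states the hypothesis as a chain. The game changes sleep habits, environment and pre-sleep activities, "and consequently (c) improve sleep parameters".
- Intergroup and Intragroups Analysis compares the arms on each outcome separately. It also plans post-minus-pre differences for all numeric variables.
- Anticipated Results says of chronotype that "different types have influences on the presence of sleep disorders and accentuate inadequate sleep habits", and adds that it was not assessed. The same section warns that parents' reports may be coloured by social desirability, and that good bedroom conditions are harder to provide in families of low socioeconomic status. The Introduction links lower income or maternal education to sleep problems in children.

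**The concern.** The hypothesis has two links: game to habits, and habits to sleep. Randomisation supports statements about what the game does to habits and to sleep. It does not by itself show that habits carry the effect. The article hands that second link to simple correlations between children and says that they bear on proving it.

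Within such a correlation, a child's habits are observed, not assigned. A non-zero r may reflect a common cause, poor sleep leading to poor habits, or the same parent answering both instruments in the same spirit. At stake is an exploratory statement of mechanism in the eventual report: a confounded correlation could be presented as evidence that applying sleep hygiene improves sleep.

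**Working it through.** **1. Which analysis addresses which link**

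| Link | Planned analysis | Protected by randomisation? |
|---|---|---|
| Game to habits | Between-arm comparison | Yes |
| Game to sleep | Between-arm comparison | Yes |
| Habits to sleep | Pearson correlations only | No |

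**2. Rival explanations in the article, and what the plan does about them**

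- Socioeconomic status: tied to sleep problems (Introduction) and to bedroom conditions (Anticipated Results). It is measured, but only correlated separately.
- Chronotype: tied to sleep disorders and to inadequate habits (Anticipated Results). It is not measured, so it cannot be adjusted for.
- Shared reporter: parents complete the hygiene scale and the sleep diary (Sleep Diaries; Design and Procedures). Social desirability is acknowledged but not handled in this analysis. Only parents in the experimental group attend the sleep workshop, which could move both reports together if arms are pooled after the intervention.
- Direction: nothing stated separates habits affecting sleep from the reverse.

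**3. How often a correlation would be significant with no causal link**

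The article gives no figure for this analysis, so there is none to reproduce. Inputs:

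- n = 2 × 88 = 176 (Participants), assuming that every child has data.
- Significance level 5% (Proposed Analysis), taken as two-sided because the sidedness is not stated.
- a and b, the correlations of a common cause with habits and with sleep. These are assumed; the article gives none.

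Smallest significant correlation, with t = 1.974 on 174 degrees of freedom:

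r = 1.974 / √(174 + 1.974²) = 1.974 / 13.338 = 0.148.

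If habits have no effect on sleep, the induced correlation is r = a × b. By the Fisher approximation, z = atanh(r) × √173, and the chance of significance is 1 − Φ(1.96 − z) + Φ(−1.96 − z).

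| a = b (assumed) | Induced r | z | Chance of significance |
|---|---|---|---|
| 0.2 | 0.04 | 0.53 | 8% |
| 0.3 | 0.09 | 1.19 | 22% |
| 0.4 | 0.16 | 2.12 | 57% |
| 0.5 | 0.25 | 3.36 | 92% |

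The nominal rate is 5%. An observed r of 0.25 would give t = 0.25 × √(174 / 0.9375) = 3.41, p = 0.0008.

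**4. Pooling the arms**

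Suppose the game shifts habits and sleep independently, each by d within-arm standard deviations, with no habit-to-sleep link within arms. Pooling equal arms induces r = (d²/4) / (1 + d²/4).

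- d = 0.5 (the effect size in Participants): 0.0625 / 1.0625 = 0.059, significant about 12% of the time.
- d = 0.8 (assumed): 0.16 / 1.16 = 0.138, significant about 45% of the time.

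A pooled correlation can thus arise from the game itself without habits being the route.

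**The case against.** The best defence is that the analysis is labelled exploratory and the wording is hedged: the correlations supply information, and habits may improve sleep. The claim about the game already rests on the between-arm comparison. A condensed article can leave the time point and covariates of an exploratory analysis to a fuller plan. All of this stands and keeps the point small. It does not rescue the sentence, which states a method and then an inference that the method cannot carry.

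Several stronger readings are tempting but not supported:

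- *The Introduction names common causes of the child's habits and sleep.* Its list, beginning with "influence of socioeconomic status (SES) in functionality and environment", explains why children's sleep tracks parental sleep and family functioning. The firmer sources are the later Introduction text on low socioeconomic status and Anticipated Results.
- *The correlation is built in by overlapping items.* The article says that "the scale contains five questions to evaluate bedtime resistance and daytime somnolence", but introduces these apart from the four hygiene indicators and does not say that they enter the hygiene score.
- *Shared reporting affects every correlation.* It affects the scale with the diary. Sleep is also measured by actigraphy and child-rated sleepiness, and children describe their own bedroom and bedtime activities.
- *Pearson is wrong for ordered classes.* The section mentions income and education levels, without saying how they will be scored. Rank correlation here is largely a preference.
- *A null trial result would make the habit-to-sleep statement false.* These are different hypotheses. A null comparison of the game would not settle whether habits affect sleep.

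**Conclusion.** The point holds as a minor one. The article assigns the causal step from habits to sleep to unadjusted correlations, while naming rival explanations that those correlations cannot exclude. Under pure confounding, the chance of a significant result at n = 176 runs from about 8% to 92% as the assumed common-cause correlations run from 0.2 to 0.5. The top of that range is no more likely than the rest, because the article gives no confounder strength. The figures also assume complete data and two-sided testing.

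A reader might infer that the trial's evidence for the game is compromised. It is not: the randomised between-arm comparison is unaffected, and only the exploratory conclusion about habits and sleep needs to be weakened.

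**What to change.** 1. Replace the wording about proving the hypothesis with *explore the association between sleep habits and sleep*, and draw no causal conclusion from it.
2. Use the post-minus-pre differences already planned to relate change in the hygiene score to change in actigraphy sleep measures. This removes stable differences between children, so far as their effects are constant over time. It also removes the shared reporter, except where diary entries help to interpret the actigraphy record. If the bedtime-resistance and somnolence items are scored in the hygiene total, leave them out here.
3. Show the result within arms as well as pooled. The pooled version can reflect the game acting separately on both variables. The within-arm version avoids that but is purely observational. Adjusting for arm and class together is doubtful, because Design and Procedures first assigns whole classes to arms and the two may not be separable.
4. Adjust for baseline values and socioeconomic status, and state unmeasured chronotype and possible reverse direction as limitations.

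The cost is a little more analysis and a weaker claim. No new data are needed.

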## Anticipated Results

Considering the constellation of significant and negative consequences of sleep alterations for children’s overall quality of life, the objective of this protocol of study is to verify potential effects of the serious game “Perfect Bedroom: learn to sleep well” in improving sleep hygiene habits, which includes recommendations in sleep environment, sleep routine, and daytime activities, and, consequently, the promotion of better sleep. If this protocol is effective it will be an answer of translational empirical research into effective actions (Gruber et al., 2016), presenting one way for optimizing sleep hygiene practices with children by using a serious game, preventing a series of impacts of inappropriate sleep on health, cognition and the risk at psychiatric conditions.

Poor and insufficient sleep is still an “invisible risk” and many parents and professionals underestimate children’s sleep problems. Conversely, recommendations of a sleep routine and a consistent sleep schedule are currently associated with improved sleep onset-latency and sleep consolidation, while delayed bedtime reduces the number of hours available to sleep, since children are not allowed to sleep in the morning due to school or the parent’s schedules. This recurring delay and consequent sleep loss impacts on mood, cognition, appetite and in prolonged daytime naps (Komada et al., 2011; Kitamura et al., 2015).

With the improvements in technology there is also an increase in the use of media for entertainment and work. This context is no different for children and some specialized organizations are beginning to create recommendations on limits to the use of technologies by age, however, there are still no recommendations that also consider the content and purpose of the activity developed in electronics devices (Baranowski et al., 2016; Van Rooij et al., 2017).

Presence of electronic media in the bedroom (e.g., television, video game, and computer) and the use of them next to bedtime are related to late bedtime and decreased sleep duration. In addition, children that sleep next small screens (e.g., smartphones) relate impacts in perception of insufficient rest, probably caused by waking up due to notifications on the small screen (Cain and Gradisar, 2010; Falbe et al., 2015). The opposite is also true, and children that do not have electronics in the bedroom report more hours of sleep. Other factors related to the bedroom are also relevant, such as providing a comfortable bedroom and conditions to sleep, but this is challenging for families of low SES (Chung et al., 2014; Bagley et al., 2015).

Our serious game includes recommendations in sleep environment, but just the game is not enough to help children in families with low-incomes. Provide conditions, such as quiet and dark bedroom and comfortable bed, depends on the neighborhood that the families live and their incomes. Thus, subsequent interventions should include actions to help these families provide a comfortable bedroom, such as Time’s Beds for Kids in EUA (Mindell et al., 2016).

It stands-out that in Brazil did not exist, in our knowledge, any questionnaire adapted and validated to evaluate the chronotype of children with ages between 7 and 8 years, as different types have influences on the presence of sleep disorders and accentuate inadequate sleep habits (Jafar et al., 2017), so chronotype influence was not assessed in this protocol.

Other pitfall that could be noted, is the consideration that parent’s reports may be influenced by social desirability, indicating good sleep hygiene practices instead of the real situation. Another important challenge is to promote parental involvement, since previous researches indicated a decrease in participation over the evaluation periods (Jones et al., 2013; Wilson et al., 2014; Mindell et al., 2016). In this way, we proposed follow-up meetings with parents to minimize this decrease on participation.

Although in this protocol efficacy measures in evaluation will be limited to sleep habits and patterns, the promotion of optimal sleep has consequences in multiples domains (e.g., cognitive, health, temperament) that are sometimes completely forgotten in sleep programs interventions (Blunden, 2017). Thus, future studies should include other outcomes to evaluate efficacy, such as cognitive and academic performance.

Therefore, the confluence of these factors, problems related to sleep and insufficient sleep, and the absence of adequate intervention or treatment are associated in the short and long term with negative impacts on overall health and performance. In this way, sleep hygiene practices may promote healthy sleep in children, which could influence in health outcomes and decrease the social burden of treatments. Our serious game could be applied in clinical, educational settings to promote good sleep hygiene in children and prevent these negative consequences. In addition, “Perfect Bedroom” could be applied at home with supervision of parents becoming a approach less costly compared to others cognitive and behavioral interventions used to improve sleep in children, also, reducing burdens to treatments of negative consequences of inappropriate sleep on children’s normal developmental.
